## Abstract

**Background:**

Previous research has suggested that school-based physical activity (PA) interventions may have a positive impact on academic performance. However, existing literature on school-based interventions encompasses various forms of PA, spanning from vigorous intensity PA outside the academic classes to light intensity PA and movement integrated into academic learning tasks, and results on academic performance are inconclusive. ACTIVE SCHOOL will implement two different PA interventions for one school year and assess the effects on the pupils’ academic performance, with math performance as the primary outcome.

**Methods/design:**

The ACTIVE SCHOOL project consists of two phases: 1) Development phase and 2) Randomized Controlled Trial (RCT). In phase one, two interventions were developed in collaboration with school staff. The two interventions were tested in an 8-weeks feasibility study. In phase two, a RCT-study with three arms will be conducted in 9-10-year-old children for one school year. The RCT-study will be carried out in two intervention rounds during the school years 2023/2024 and 2024/2025. Schools will be randomized to one of two interventions or control;1) *Run, Jump & Fun intervention* (4 × 30 min/week of moderate-to-vigorous physical activity; 2) *Move & Learn intervention* (4 × 30 min/week focusing on embodied learning in math and Danish lessons); or 3) a control condition, consisting of normal teaching practices. Outcome measures include academic performance, PA level, cognitive functions, cardiorespiratory fitness, anthropometry, well-being and school motivation (collected before, during and after the intervention period). A process evaluation will be conducted to assess implementation.

**Discussion:**

The ACTIVE SCHOOL study will expand knowledge regarding the impact of PA on academic performance. The study will have the potential to significantly contribute to future research, as well as the scientific and educational debate on the best way to implement PA to support education and learning.

**Trial registration:**

The study was registered on the 25th of October 2022 in ClinicalTrials.gov, NCT05602948.

**Supplementary Information:**

The online version contains supplementary material available at 10.1186/s12887-024-04647-9.

## Background

Academic performance is important both in formal education and for success later in life [1]. At the individual level, academic performance is affected by several factors and underlying mechanisms, including brain structure and function, cognitive function, mental health and well-being, school motivation, and school attitude [2, 3]. Furthermore, emerging evidence suggests positive associations between physical activity (PA), aerobic fitness, and academic outcome in children and adolescents [3], and several school-based studies have found that enhancing PA in schools can improve academic performance [4–8].

The physiological mechanisms by which PA affects academic performance are representing a rapidly growing area of multidisciplinary research. Animal models provide cellular and molecular explanations for altered brain function after PA training, and imaging models on humans show how specific brain structures are affected by PA [9, 10]. In children, some studies have found both acute and chronic benefits of PA on cognitive and academic performance [11–13]. This research has primarily used cross-sectional study designs or been conducted in highly controlled laboratory-based or after-school settings focused on the quantitative aspects of PA such as intensity, frequency, and duration. This body of research has been summarized in several reviews concluding that most studies report either a positive relation of PA to academic performance, or no relationship between these constructs [2, 7, 11–15]. The positive relationship between PA and academic performance has also been demonstrated in school-based interventions lasting one-to-three years with a PA dose ranging from 60 to 120 min of extra moderate-to-vigorous PA (MVPA) per week [16–18]. In school settings, this type of PA has often been conducted outside of the academic sessions, such as before or after lessons, during PA breaks or at recess [7, 11, 13, 19].

An emerging line of research is rooted in embodied cognition theory, characterized in the education field as “embodied learning”. This research line focuses, for example, on gestures and bodily engagement closely related to and integrated into curricular learning tasks [20], and suggests that forming actions with the body can lead to the construction of enhanced mental representations that positively affect memory recall [21, 22]. This theory suggests that sensory-motor experiences can be linked to the cognitive processes involved in complex problem-solving and strategy use, and therefore, that PA can play a crucial role in the knowledge retention and retrieval [23–25]. This line of research has focused on the qualitative aspects of PA, such as cognitive and coordinative demands [26–28]. Some school-based studies have shown promising results on academic performance following interventions containing elements of embodied learning [4, 29, 30].

Therefore, the overall aim of the ACTIVE SCHOOL study is to investigate the effects of these two different types of PA interventions (MVPA and PA integrated in the learning tasks) on academic performance in Danish children aged of 9-10-years-old (3rd grade). Due to the challenge of implementing PA in schools, both interventions have been co-developed with school staff, as recommended [31]. The design phase is described in more details and published elsewhere [32]. Prior to commencing the randomized controlled trial (RCT), an 8-week feasibility study was set up to evaluate the implementation of the two interventions, and the feasibility of the proposed test battery for the RCT [33] Accordingly, the aim of this protocol is to summarize knowledge and experiences from the development phase, and to introduce the rationale and design of the cluster RCT-study.

## Methods

The ACTIVE SCHOOL study consists of two phases: 1) The Development phase including the design phase and feasibility testing of the two PA interventions, and 2) the RCT investigating the effects of the interventions. The two phases of ACTIVE SCHOOL study are illustrated in Fig. 1.

**Fig. 1 Fig1:**
[figure not shown]
Phases and timeline in the ACTIVE SCHOOL study

### Design phase

The ACTIVE SCHOOL study’s design phase was conducted from May 2021 until June 2022 and is published elsewhere [32]. It was guided by McKenney and Reeves´ *Generic Model for conducting research in education* [34]. This model integrates theory, research, and practice into one model. The model comprises three core phases 1) Exploration and Analysis, 2) Construction and Design, and 3) Reflection and Evaluation. The two PA interventions ‘*Run, Jump & Fun*’ (RJF) and ‘*Move & Learn*’ (ML) were designed in collaboration between researchers and school staff, and the results were the intervention principles presented in Table 1. The intervention dose were defined as 30 min of PA delivered four times per week, with several implementation strategies to facilitate adoption and practice of the interventions [35].

**Table 1 Tab1:** Principles of ‘*Run, Jump & Fun*’ and ‘*Move & Learn*’ interventions developed throughout the design phase and based on in-school testing, observations, and reflections in the researcher team

RJF principles	ML principles
• Connect a pedagogical aim to the RJF activity. • Pay attention to the target group and prepare activities in advance. • Instructions must be short and precise. • Modify the activities, so inactive breaks do not occur. • Be aware of the duration and intensity of activities. • Foster the possibility of autonomy in activities. • Discover opportunities for activities in alternative settings.	• Integrate curriculum-based PA in two Danish and two Math lessons per week. • The bodily engagement must underpin the curricular aim of the lesson. • The body can and must be a part of the immersion or the solution of an academic activity during the intervention time. • Organize group activities with a maximum of three members in each group. • Foster the possibility of autonomy in activities.

### Feasibility study

As recommended before performing an effect study, implementation outcomes (e.g., acceptability and feasibility) of the two interventions were assessed during an eight-week feasibility study conducted between September and November, 2022 [33, 36] (will be reported elsewhere – manuscript under preparation).

The aims of the feasibility study were to: 1) Investigate implementation outcomes of the RJF and ML interventions and, 2) Test the preliminary test-battery for the RCT-study.

The feasibility study resulted in the final definition of the two interventions, including principles, strategies, course designs, dose and frequencies (see *Intervention conditions* and *Training of school staff*). During the feasibility study the test-battery was tested at four schools to ensure that the final battery was applicable for the RCT, considering logistical factors such as resources, test days, duration, and feasibility. The feasibility of the test loop during the test day was examined, leading to necessary adjustments. Furthermore, optimization and standardization of test procedures were assessed, considering the duration of the testing process. Adjustments were made after the feasibility study, refining the test schedule, supplementing academic and executive function tests, and standardizing equipment for anthropometry in preparation for the RCT. Various approaches were explored for standardized academic outcomes, including evaluating mathematical tests for second and third-grade students to determine the appropriate academic level for the RCT. Teachers were found to be capable of conducting standardized academic tests.

During the feasibility study, challenges occurred in managing data across paper and various software platforms. To address this, we implemented REDCap (see *Methods, Outcome Measures*) to streamline data collection and handle extensive datasets.

### Randomized controlled trial (RCT)

The overall aim of the ACTIVE SCHOOL RCT study is to investigate the effects of two different types of in-school PA interventions on academic performance in children aged 9–10 years (3rd grade). The cluster RCT has three arms and includes two intervention groups; (1) RJF and (2) ML, and (3) control group (CG). The interventions are planned for one school year carried out in two rounds during the school years 2023/2024 and 2024/2025. The randomization will be stratified at the school level with an approximate 1:1:1 recruitment protocol (RJF:ML:CG). Approximately nine schools will be allocated to each arm (see *Randomization*). Due to the study design, blinding of instructors, teachers and participants will not be possible, which is common practice in school-based studies.

Schools from all regions of Denmark will be recruited by phone, e-mail, relevant websites, and digital/social media targeting school staff and school principals. If principals and school staff agree to participate in the study, an informal project meeting will be held, and comprehensive information will be provided.

#### Intervention conditions

##### Run, Jump & Fun intervention

RJF consists of four sessions of 30 min of MVPA each week for one school year. RJF must be conducted on all school days except the day timetabled with mandatory Physical Education (PE).

During two initial process meetings, the RJF intervention is established and tailored to fit the local school structure. ACTIVE SCHOOL project personnel, school principal and school staff take part in this establishing process, before the beginning of the intervention. RJF sessions can be placed in different time slots during the day, and should be delivered by either PE teachers, teachers from other subjects or the school’s pedagogical personnel (pedagogues). The intervention deliverers must engage in all RJF training and use the intervention materials (see below).

Besides the duration and intensity requirements, an additional aim of RJF activities is that they are fun, motivational, and inclusive for all children, regardless of academic skills, PA, fitness or motor skill level. To achieve this aim a motivational environment supportive of children’s´ needs will be created, as outlined in the self-determination theory [37]. The delivery of the intervention and practice with RJF will be guided by the seven principles developed in the design phase (see Table 1).

Examples of RJF activities include ball games in small teams, relay and obstacle run, martial art games or dance. RJF can be conducted in various settings depending on the individual school. Typically, RJF will take place in either the classroom or adjacent indoor spaces, or outdoor spaces (e.g. in the schoolyard, or in the gym hall).

##### Move & Learn intervention

ML consists of four sessions of 30 min of Physical Active learning (two math lessons and two Danish lessons) every week for one school year. ML will be conducted on all school days except the day timetabled with PE. All 3rd grade classes in the Danish school system have a minimum of four lessons (45 min each) of math and six lessons of Danish each week. ML lessons will be conducted in the classroom, adjacent spaces in the school building, outdoors in the school yard, or in the local environment. One initial process meeting with ACTIVE SCHOOL project personnel, school principal and school staff is held at each ML intervention school to establish and tailor the intervention to the local school structure.

ML is delivered by Danish and math teachers, who must engage in all ML training and use the intervention materials.

All ML lessons should focus on embodied learning, with a close connection between the academic learning task and bodily engagement. ML activities aim to be fun, motivating and foster mastery of the subject matter among the children. ML is guided by five principles developed in the design phase (see Table 1).

In ML activities could, for example, be group work dramatizing verbs with the whole body while reading a story out loud, using big grids in the school yard and let the children play an active figure in a coordinate system, or discovering ambience in a novel, by visiting and exploring places that sound, smell or feel like the place described by adjectives in the novel. Integration of the body in learning tasks can vary. It can be physical or motor-skill demanding activities, or it can be less vigorous activities, even standing up miming, using hand gestures or facial expressions.

##### Both interventions

To support implementation, school principals should agree to allocate 22 h to each teacher/pedagogue involved in delivering the interventions and 32 h for one teacher to coordinate with ACTIVE SCHOOL, e.g., set dates for courses and testing. Every teacher or pedagogue involved in the project will have these hours prioritized in their teaching load (their planned tasks during the year) to be able to participate in project training and meetings.

As a strategy to sustain the interventions for a whole year, each school organize school staff meetings about the intervention every second month to plan and share experiences about the intervention. Meeting agendas and guides will be provided by the ACTIVE SCHOOL project group. These meetings must be supported by school leaders who can attend or get minutes from the meeting.

#### Training of school staff

Teachers and pedagogues receive specific training for delivering either RJF or ML interventions. The training is conducted by educators from University College Copenhagen teacher education and pedagogue education. To ensure the sustainability of the interventions, a gradual introduction to the intervention principles has proven effective in previous studies [38–40]. Therefore, a gradual introduction will be applied in both interventions.

The RJF teacher training program includes a 6-hour introduction course held at a central location for all schools before the intervention starts, a 3-hour follow-up course held at each school after 2 months, and a 5-hour thematic follow-up course held at a central location for all schools after 6 months.

The ML teacher training program includes a 6-hour introduction course held at a central location for all schools before the intervention starts, a 3-hour follow-up course held at each school after 2 months, a 2-hour thematic follow-up course held in hybrid formats (on-site or online) at local schools after 4 months, and a 3-hour advanced course held at a central location for all schools after 7 months.

In both interventions, school staff are expected to organize internal team-meetings in the months without planned courses. These serve to maintain focus throughout the whole intervention period. A reflection paper will guide the internal staff-meetings in common reflections regarding progression and delivery of the interventions.

#### Control condition

The control schools will continue their normal practice but take part in all baseline- and post-testing of primary and secondary outcomes.

#### Recruitment of participants

Once schools agree to participate, all children and parents or legal guardians in participating classes will receive written information and consent forms from the research team. For a child to participate in the scientific measurements the parents/legal guardians must return a written informed consent prior to baseline measurement, but all children from intervention schools will participate in the intervention activities (See fig. 1: Phases and timeline in the ACTIVE SCHOOL study). Participation in the project is voluntary and free of charge, and it is possible to withdraw consent at any time without giving a reason.

There are no exclusion criteria for children in the participating classes. It is unlikely that adverse events and other unintended effects of the interventions will occur when using the described scientific methods. In the rare cases where incidental findings, like mis-thriving and anxiety may occur, the person responsible for the research will contact the school for further contact to parents/guardians and relevant authorities.

#### Randomization

An independent statistician employed at the Department of Mathematics, University of Copenhagen, facilitated the process of randomizing the participating schools into three groups. The statistician utilized the open-source software R and the sample function to generate a randomized list of numbers for the 27 schools. To ensure a balanced stratification, we sequentially assigned numerical labels to the schools based on their receipt of written consent for participation. The statistician remained unaware of the intervention content and the true identities of the schools. The schools enrolled in the study for the school year 2023/24 were informed of their assigned groups before the summer holiday starting in June 2023 and new schools for the school year 2024/25 will be informed before summer holiday 2024.

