#### Plan for data management, analysis, and statistics

Descriptive statistics across groups will be summarized and presented. Flow diagram of participants will be described and presented according to the Consolidated Standards of Reporting Trials (CONSORT) 2010 for randomized controlled trials [64]. Differences at baseline between participants included and excluded in the main analyses will be presented (e.g., drop-out analyses) and data will be analyzed for between-group differences (interventions vs. control) at baseline for all outcomes. The effects of the intervention on both primary and secondary outcomes will be tested in intention-to-treat analysis using multilevel mixed models with group (interventions/control) as fixed effect and adjusted for relevant confounders not evenly distributed between groups at baseline. School and class will be included as random effects in the model to account for the cluster structure of the data. Furthermore, per-protocol analysis will be performed including only children from classes compliant with the intervention principles (based on SMS-survey answers from teachers/pedagogues). The statistical analysis will be performed using R (R Core Team, 2022) and in the IMB Statistical Package for the Social Sciences (SPSS) version 24.

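### The randomisation is described as stratified and balanced, but the procedure given has no stratum, and school-year round is pre-specified neither in the allocation nor in the models

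*Protocol article*

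**What the plan says.** Two sections of the protocol article describe the allocation. The section Randomized controlled trial (RCT) states: "The randomization will be stratified at the school level", in an approximate 1:1:1 ratio, and adds: "Approximately nine schools will be allocated to each arm". It names no stratifying variable. The section Randomization gives the mechanism. An independent statistician "utilized the open-source software R and the sample function to generate a randomized list of numbers for the 27 schools", and the purpose of the labelling is explained as: "To ensure a balanced stratification, we sequentially assigned numerical labels to the schools based on their receipt of written consent for participation". No blocks, strata or separate lists are mentioned.

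The trial runs in two cohorts of schools: "The interventions are planned for one school year carried out in two rounds during the school years 2023/2024 and 2024/2025". The Randomization section treats the 2024/25 schools as new ones, told their group a year after the first cohort. The number of schools per round is not given.

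Two sections describe the model. Sample size and power has the baseline value plus school and class as random effects. Plan for data management, analysis, and statistics has group as the fixed effect, adjustment for confounders found to be uneven between groups at baseline, and this random part: "School and class will be included as random effects in the model to account for the cluster structure of the data". Round or school year is named in neither.

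**The concern.** The article attributes to its procedure a property that the procedure does not have. Stratified randomisation means separate, restricted allocation within levels of a named variable. Here the only ordering is by consent date, and a random permutation removes any effect of that ordering. Sample size and power identifies schools as the units randomised, so stratifying at the school level has no meaning as written. A results paper that repeated the word would misreport the design.

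The gap matters mainly for round. The two rounds differ in cohort of children, school year and the project's experience of delivery. With about nine schools per arm, chance can leave the arms visibly uneven by round. The models as described do not fix in advance how that would be handled.

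**Working it through.** **Plan's own figures.** Three arms of nine schools give 3 × 9 = 27, which agrees with the total stated. Whether nine per arm meets the stated power is a separate matter and is not needed here.

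**Inputs.** From the documents: 27 schools, three arms of nine, two rounds, planned effect 0.42, intraclass correlation 0.15, 20 children per class and at least one class per school. Assumed, because not stated: the number R of schools in round 1 (9 to 18), and a round effect δ on math left after baseline adjustment (0.1 to 0.3 SD).

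**Step 1: chance imbalance by round.** If 27 labels are shuffled once into 9/9/9, the numbers of round-1 schools in the arms (a, b, c, with a + b + c = R) follow a multivariate hypergeometric distribution:

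P(a, b, c) = C(9,a) · C(9,b) · C(9,c) / C(27,R).

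Summing over the relevant outcomes:

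| Round split | One given intervention v control differ by ≥ 3 | Any two of three arms differ by ≥ 3 | All arms within 1 |
|---|---|---|---|
| 9 / 18 | 0.220 | 0.386 | 0.126 |
| 12 / 15 | 0.244 | 0.425 | 0.115 |
| 13 / 14 | 0.247 | 0.501 | 0.299 |

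The first probability column fits the planned comparisons of intervention with control. The second also counts the two interventions against each other. Allocation restricted within round would hold every difference to at most one school. A single shuffle achieves that only 12% to 30% of the time.

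**Step 2: what a three-school difference does.** With schools of equal size and no round term, the contrast picks up (a − c)/9 × δ. For a − c = 3 this is δ/3:

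- δ = 0.1: 0.033 SD, and 0.033/0.42 = 8% of the planned effect
- δ = 0.2: 0.067 SD, 16%
- δ = 0.3: 0.100 SD, 24%

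**Step 3: set against sampling error.** With one class of 20 per school and no baseline adjustment, the variance of a school mean is 0.15 + 0.85/20 = 0.1925. The standard error of a contrast of nine schools with nine is √(2 × 0.1925/9) = 0.207. The shift at δ = 0.2 is 0.067/0.207 = 0.32 of a standard error.

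**Step 4: precision.** In an even split, an unmodelled round effect adds δ²/4 to the between-school variance. At δ = 0.2 this is 0.01, and 0.01/0.1925 = 5% of variance, or √1.052 − 1 = 2.6% of the standard error. At δ = 0.3 it is 0.0225, which is 12% of variance and 5.7% of the standard error.

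**The case against.** Several points on the other side stand in whole or in part.

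- **Chance imbalance is not bias.** A reader might infer that round is systematically confounded with arm. It is not. Under a random shuffle round is independent of arm in expectation, and the school random effect carries the extra variance into the standard error. What is lost is precision and protection against an unlucky draw.
- **Baseline adjustment helps.** It removes much of a round difference already present at the start of the year. It does not remove a difference that arises during the year, for example from greater experience of delivery.
- **Round could still enter the model.** The clause on confounders uneven at baseline would admit it, and an analysis plan that is not shown may name it. On the article's text, however, the route is a choice made after looking at the data, when a stated term is free of that objection.
- **A single shuffle is an inference.** The article does not say how list numbers were mapped to arms. Blocks along the consent order, or a separate list per round, would give some balance over time. If either was used, the description needs to say so.
- **Concealment.** A reader might also infer that the arms of second-round schools were foreseeable, because one list covers all 27 and the research team numbers schools as they consent. The documents do not support this. Nothing says that the team held the unused part of the list. An independent statistician unaware of the schools' identities produced it, and custody of the list is the kind of detail that an article leaves to the full protocol.

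**Conclusion.** The point holds in a limited form. The claim of a stratified, balanced randomisation is not supported by the procedure described; this rests on the text alone and needs no assumption. The consequence is moderate: a 22% to 25% chance of a three-school or larger gap by round between a given intervention and control, and then a shift of about 0.03 to 0.10 SD in the contrast.

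The probabilities assume one shuffle into exactly 9/9/9 and a round split between 9/18 and 13/14. The shifts assume a residual round effect of 0.1 to 0.3 SD, for which the documents give no figure, and schools of equal size. The validity of the randomisation is not in question. The correction is worth making because the wording is wrong and the remedy costs almost nothing.

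**What to change.** 1. In both sections that describe the allocation, delete the claim of stratification and of balance through consent-order labelling, and describe the scheme as an unstratified random allocation of schools. If a stratum or per-round lists were in fact used, name the stratum and describe the lists instead. Cost: wording only.
2. Pre-specify round (2023/24 or 2024/25) as a fixed effect in the primary and secondary outcome models, both in Sample size and power and in the statistics section, so that its inclusion does not depend on observed imbalance. Cost: one degree of freedom. At school level that leaves 27 − 3 − 1 = 23 rather than 24.

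A fresh 1:1:1 draw for the second round is not recommended as a general remedy. If round 1 had fallen 6/4/3, a new 5/5/4 draw of the remaining 14 schools could end at 11/9/7, below the planned nine in one arm. The existing list would end at 9/9/9. Any within-round allocation of schools not yet allocated must therefore keep the planned total of nine per arm. Steps 1 and 2 remain possible even if all schools are already allocated.
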